**Methods/Design:**

This is a single-center, randomized controlled trial (RCT) with a 3-month follow-up. Usual care plus a 12-week supervised exercise program will be compared to usual outpatient care alone. The primary outcome will be patient autonomy measured by the Camberwell Assessment of Need (CAN) schedule – clinician rated. Secondary outcomes include cardiovascular risk factors, cognitive functioning, substance abuse, body awareness, depression and mood state. Changes in inflammatory markers and microbiotica will be explored. The feasibility of using patients as exercise trainers will also be assessed.

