### Participants

The study will include 80 patients: 40 will receive the exercise intervention, and 40 will serve as active (wait-list) controls. Both new and existing patients will be invited to participate.

Inclusion criteria: All patients attending the clinic with a diagnosed first-episode psychotic disorder who provide informed consent and wish to participate will be included.

Exclusion criteria: Patients with severe somatic disorders or injuries that make it difficult or unsafe to exercise will be excluded. Patients with a history of cardiovascular disease and pregnant women will also be excluded.

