### Screening interview

A research assistant or nurse will initially perform a brief screening interview at the clinic to determine patient eligibility using the criteria outlines above. Suitable patients will then be invited to participate in the trial, informed consent obtained, and a baseline assessment conducted prior to randomization.

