### Statistical analysis

Participant characteristics, stratified by treatment group (exercise versus active control) will be presented. Baseline differences will be tested using t-tests for continuous variables and Chi-square tests for categorical outcomes. Parametric test assumptions will be examined and reported. Nonparametric data will be transformed or alternatively analyzed using nonparametric statistical tests. Multiple imputation will be used to replace missing internal values where appropriate. Within-group changes in the primary outcome (autonomy) and secondary outcomes (health, cognitive ability, substance use, etcetera) will be analyzed using paired sample t-tests. To address the primary research question, intention-to-treat analyses will be performed. The effect of group allocation on autonomy and all secondary outcomes at 3 month follow-up will be assessed using linear regression models (logistic for binary outcomes), using both the mean difference (baseline to 3 months) and total scores as dependent variables. Where the total score is used as the outcome, baseline group differences in covariates will be adjusted. Data from individual accelerometers will be pooled to objectively assess changes in physical activity levels before and after treatment. All analyses will be performed using SPSS 22.0. All tests will be two-sided and *P*-values of less than 0.05 will be considered statistically significant.

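### The total-score model adjusts for observed baseline differences instead of named covariates, so baseline CAN would usually be left out, at a cost in precision and power

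*Protocol article*

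**What the plan says.** The primary outcome is named in the Abstract (Methods/Design): "The primary outcome will be patient autonomy measured by the Camberwell Assessment of Need (CAN) schedule", clinician rated. Baseline is measured before allocation; the Screening interview section has "a baseline assessment conducted prior to randomization". The Participants section gives the size: "The study will include 80 patients: 40 will receive the exercise intervention, and 40 will serve as active (wait-list) controls".

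Three statements in the Statistical analysis section matter here:

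- On the baseline comparison: "Baseline differences will be tested using t-tests for continuous variables and Chi-square tests for categorical outcomes". The section closes by making every test two-sided at the 0.05 level, which takes in these tests too.
- On the between-group models, for autonomy and all secondary outcomes: linear regression (logistic for binary outcomes), "using both the mean difference (baseline to 3 months) and total scores as dependent variables". Neither is named as the main one.
- On covariates: "Where the total score is used as the outcome, baseline group differences in covariates will be adjusted". No covariate is named for either model.

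**The concern.** Baseline precedes randomisation and allocation is done externally, so any baseline difference between arms is due to chance. A significance test of that difference answers no useful question. If its result decides what is adjusted for, covariates are picked by how unbalanced they happen to be and not by how well they predict the outcome. Baseline CAN, the obvious predictor of later CAN, would then be left out of the total-score model in most trials, while a variable unrelated to outcome could enter by chance.

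Two things are at stake. In a trial with a moderate but non-significant imbalance in baseline CAN, part of that imbalance remains in the total-score estimate. In nearly every trial, the precision that a score already collected would bring is given up. The covariate set also becomes known only once baseline data by arm have been seen.

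**Working it through.** The article gives no SD, effect size, power or baseline-outcome correlation, so there is no stated figure to reproduce.

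**Inputs from the article:** 40 per arm; two-sided 0.05.

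**Assumptions:** correlation rho between baseline and follow-up score of 0.3, 0.5 or 0.7; true effect of 0.5 SD for power; normal data with equal variances; baseline CAN as the only candidate covariate.

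**Step 1. Largest imbalance that is not significant.** t(0.975, 78) × sqrt(2/40) = 1.991 × 0.2236 = 0.445 SD. Under sound randomisation the test is significant in 5% of trials, so baseline CAN is left out in the other 95%.

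**Step 2. Carry-over at that limit.** The unadjusted difference is shifted by rho × 0.445:

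- rho 0.3: 0.13 SD
- rho 0.5: 0.22 SD
- rho 0.7: 0.31 SD

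The standard error of the unadjusted difference is sqrt(2/40) = 0.224 SD, so these shifts are 0.6, 1.0 and 1.4 standard errors.

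**Step 3. Simulation.** The rule of adjusting only if the baseline t-test gives p < 0.05 was compared with always adjusting (ANCOVA) and with the unadjusted change score, using 40,000 trials per setting.

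| | rho 0.3 | rho 0.5 | rho 0.7 |
|---|---|---|---|
| Type I error over all trials, rule | 4.8% | 4.3% | 3.6% |
| Power at 0.5 SD, rule | 60% | 60% | 61% |
| Power at 0.5 SD, always adjusting | 63% | 71% | 87% |
| Power at 0.5 SD, change score | 46% | 60% | 81% |

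At rho 0.5 the standard error is 0.216 SD under the rule and 0.195 SD with adjustment in every trial.

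**Step 4. Trials with a moderate, non-significant imbalance.** About 13% of trials have a baseline difference of 0.30 to 0.445 SD in one direction or the other. Where it lies in a given direction, the mean error under the rule is 0.11, 0.18 and 0.25 SD in that direction, and the type I error is about 6%, 9% and 12%. With baseline always included, the mean error is about 0 and the type I error about 5%.

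**Step 5. Chance entry of other variables.** With 10 to 20 independent baseline variables (an assumed number), the chance of at least one significant difference is 1 − 0.95^10 = 40% to 1 − 0.95^20 = 64%, whether or not the variable is prognostic.

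**Step 6. Change-score model.** It subtracts the whole baseline difference where only the fraction rho should be removed. At the 0.445 SD limit its error is (rho − 1) × 0.445 = −0.31, −0.22 and −0.13 SD, opposite in sign to Step 2.

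**The case against.** **The selection rule is inferred.** The testing sentence follows the one on presenting participant characteristics and may serve only the baseline table. The adjustment sentence comes later and mentions neither significance nor a threshold. It could even be a loose way of saying that baseline is brought in where the change score does not already contain it. This stands as a limit on certainty: a reader might infer that the article expressly ties covariates to p-values, and it does not. But the section offers no other criterion, and judging differences by size would still let the data choose the model.

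**The change-score model always uses baseline.** True, and the two estimates err in opposite directions around the ANCOVA answer. At rho 0.7 the change score recovers much of the lost power (81% against 87%). At rho 0.3 it does worse than the rule (46% against 60%). It therefore softens the problem at high correlation but does not cure it.

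**False positives.** A reader might infer that the rule inflates the trial's type I error. It does not: over all randomisations the rule is slightly conservative. A rate of about 13% (rho 0.5) or 20% (rho 0.7) arises only for an imbalance just under the threshold (baseline z = 1.95), and at rho 0.3 the same calculation gives about 8%. Those edge values do not describe the trial as a whole.

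**Knowledge of allocation.** A reader might also infer that an unblinded analyst will choose the model. The article says that assessors will mostly know the allocation; it says nothing on this about the analyst.

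**A condensed article may leave a covariate list to the full plan.** That would excuse silence. Here a rule is stated, and it is the rule that is at issue.

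**Conclusion.** The point holds as one about precision, power and error in the realised trial. As written, and on the natural reading, adjustment in one of the two between-group models of the primary outcome depends on observed imbalance. Baseline CAN is then absent from that model about 95% of the time, and imbalances of up to 0.445 SD go uncorrected.

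The estimate remains unbiased on average and the overall type I error stays below 5%, so the validity of the trial is not in question. The size of the loss depends on a correlation that the article does not give. At an assumed effect of 0.5 SD, power falls short of what always adjusting would give by about 3 percentage points at rho 0.3, 11 at 0.5 and 26 at 0.7. The loss is thus small if CAN scores track weakly over time and large if they track strongly. In an 80-patient trial it is worth avoiding, since the baseline score is collected anyway.

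**What to change.** - Present the baseline table descriptively and drop the significance tests of baseline differences.
- Replace the adjustment sentence with a fixed rule: every between-group model includes the baseline value of its outcome, whatever the observed balance. For continuous outcomes this also makes the change-score and total-score models give the same treatment estimate, because subtracting a covariate that is already in the model leaves the group coefficient unchanged.
- Name any further covariate (age, for example) before data by arm are seen, and restrict it to variables collected completely. Number of admissions is a weaker candidate: under Baseline and post-treatment assessments it comes from patient files, and only where these can supply it, so forcing it into the model could create missing data.

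The cost is analysis wording only; no new data are needed.

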Inactivity is another key feature of psychosis; most individuals with the disorder do not meet the minimum physical activity levels recommended for general health [10]. This is problematic because regular exercise has positive neurobiological effects, which are likely to benefit this patient group. For example, exercise affects the hypothalamic-pituitary-adrenal (HPA) axis, which in turn modulates stress-reactivity [11, 12]. Exercise also influences hippocampal cell proliferation [13], and serotonergic release [14], producing an anti-depressant effect when performed regularly. Regular physical activity has been shown to lower systemic inflammation [15], which may be of importance in psychotic patients. According to three Cochrane reviews, physical exercise has moderate effects on depression equivalent to anti-depressant treatment [16–18]. Other beneficial effects include improved sleep quality [19] and increased neural growth factor expression, which affects neurogenesis, learning and memory [20]. Recent studies suggest that exercise may also reduce cravings for alcohol and other drugs in substance dependent individuals [21, 22]. Despite this evidence, few studies have explored the effects of exercise in patients with psychosis, a physically inactive patient group with high rates of comorbid depression and substance abuse.

The primary objective of FitForLife is to examine the effects of a 12-week physical exercise program on autonomy in young adults with psychosis. Secondary aims are to explore changes in general health, cognitive ability, substance use, body awareness, depression and mood states. Blood and feces samples will be requested to assess changes in inflammatory markers and microbiotica. The feasibility of educating patients as exercise trainers will also be assessed. We hypothesize that the intervention will lead to improvements in all outcomes assessed.

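### P<0.05 applies to every test, with two between-arm analyses per outcome and neither decisive, so the error exceeds 5% for CAN itself and more so across the secondary outcomes

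*Protocol article*

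**What the plan says.** The abstract names a single primary outcome: "The primary outcome will be patient autonomy measured by the Camberwell Assessment of Need (CAN) schedule", clinician rated. The Background makes autonomy the primary objective and words the rest as exploration: "Secondary aims are to explore changes in general health, cognitive ability, substance use, body awareness, depression and mood states". The same paragraph closes with a hypothesis for everything: "We hypothesize that the intervention will lead to improvements in all outcomes assessed".

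The Statistical analysis section treats primary and secondary outcomes alike:

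- **Scope.** "The effect of group allocation on autonomy and all secondary outcomes at 3 month follow-up will be assessed using linear regression models" (logistic models for binary outcomes).
- **Two analyses per outcome.** The models are fitted "using both the mean difference (baseline to 3 months) and total scores as dependent variables". Neither is named as the one that decides. For the total score, covariates that differ between groups at baseline are to be adjusted for; the section does not say whether the baseline value of the outcome is always among them.
- **Within-arm tests.** Changes in primary and secondary outcomes "will be analyzed using paired sample t-tests".
- **Criterion.** "All tests will be two-sided", and P-values "of less than 0.05 will be considered statistically significant". The sentence makes no distinction between primary and secondary outcomes.

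**The concern.** There are two linked problems.

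First, the primary comparison has two routes to a significant result. With change score and total score both tested at 0.05 and neither decisive, a significant result on either can be reported as the finding on autonomy. The two analyses are correlated but not identical, so the error for CAN is above the nominal 5%.

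Second, the same criterion and the same pair of analyses apply to all secondary outcomes, and the Background hypothesises benefit on each. An isolated P<0.05 on, say, one cytokine or one cognitive test can then be presented as confirming a stated hypothesis. The Background's exploratory wording points the other way, so the document gives two incompatible readings of what a secondary P-value means.

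The Discussion says the results are meant to inform clinicians and researchers about exercise as an adjunct treatment. What is at stake is whether a chance result on CAN or on a secondary measure is passed on as an established effect.

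**Working it through.** **Inputs from the article.** Two-sided criterion 0.05 for every test; two dependent variables per outcome (Statistical analysis); 40 patients per arm (Participants). The 0.05 is the only error figure stated. One test gives 5% error, of which 2.5% is in the direction of benefit.

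**Assumptions.** The article gives no correlations and no count of tests. I use a baseline to follow-up correlation r of 0.3-0.7 with equal variances, and a between-outcome correlation of 0, 0.3 or 0.5. The count is a tally of about 20 from the research questions and the assessment list: CAN, MADRS, anxiety, substance use, weight/BMI, waist, hip, blood pressure, lipids, VO2max, three inflammatory markers, three cognitive tests, body awareness, symptom recurrence, hospitalization and habitual activity. Microbiota and PANAS are left out.

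**Step 1: CAN alone, two dependent variables.**

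If the total score is not adjusted for its baseline value, the change and total-score statistics have correlation sqrt((1-r)/2). If it is adjusted, the correlation is sqrt((1+r)/2). The chance that either statistic exceeds 1.96 in absolute value follows from the bivariate normal distribution:

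| r | Correlation, unadjusted | Either P<0.05 | Correlation, adjusted | Either P<0.05 |
|---|---|---|---|---|
| 0.3 | sqrt(0.35) = 0.59 | 8.8% | sqrt(0.65) = 0.81 | 7.8% |
| 0.5 | sqrt(0.25) = 0.50 | 9.1% | sqrt(0.75) = 0.87 | 7.3% |
| 0.7 | sqrt(0.15) = 0.39 | 9.4% | sqrt(0.85) = 0.92 | 6.8% |

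So the error for CAN is about 7-9%.

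**Step 2: about 20 outcomes, one test each.**

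- Independent, either direction: 1 - 0.95^20 = 64%.
- Independent, benefit only: 1 - 0.975^20 = 40%.
- With equicorrelated normal test statistics, all outcomes scored so that higher is better:

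| Between-outcome correlation | Any P<0.05 | Any P<0.05 favouring exercise |
|---|---|---|
| 0 | 64% | 40% |
| 0.3 | 54% | 28% |
| 0.5 | 42% | 21% |

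A separate simulation of t-tests with 40 per arm (4000 runs) gave 64%, 55% and 44% in either direction, which agrees closely. The count matters: with 10 independent outcomes the figures are 1 - 0.95^10 = 40% and 1 - 0.975^10 = 22%; with 15 they are 54% and 32%.

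**Step 3: about 20 outcomes, both dependent variables.**

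- Independent, total score unadjusted, r = 0.5: 1 - (1 - 0.0907)^20 = 85%.
- Independent, total score adjusted for its baseline: 1 - (1 - 0.068)^20 = 76% to 1 - (1 - 0.078)^20 = 80%.
- The same simulation with both analyses, total score unadjusted and r = 0.6, gave 86%, 78% and 65% at correlation 0, 0.3 and 0.5. Counting benefit only, it gave 60%, 44% and 35%.

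Step 3 slightly overstates the position for any binary outcome, which would have a single logistic model. The within-arm paired tests are not counted in any step.

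**The case against.** The strongest reply is that this is mostly an absence. A two-sided 0.05 criterion is the usual nominal statement, and a journal article often leaves multiplicity for secondary outcomes to a full protocol or analysis plan, neither of which is shown. CAN is the single named primary outcome, the secondary aims are worded as exploration, and the abstract also says inflammatory and microbiota changes will be explored. With one primary outcome and exploratory secondaries, unadjusted secondary P-values are common practice. A hypothesis of benefit on all outcomes is a scientific expectation, not a rule that any one significant result proves success.

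Much of this stands. A reader might infer that nothing sets CAN apart and that every outcome carries an equal confirmatory claim. The article does not support that, because it names one primary outcome and one primary objective.

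A reader might also infer that a false claim of benefit is more likely than not. On one test per outcome it is not: the benefit-only figures are 21-40%, and 28 independent tests would be needed to pass 50%. With both dependent variables, the benefit-only simulation passes 50% at correlation 0 but not at 0.3 or 0.5, and independence is implausible for measures such as weight, waist and hip taken in the same patients. Nor should the 85% be read as the error of the plan, since it assumes independence, a tally of 20 and no baseline adjustment.

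What does not stand is the claim that the matter is merely left open. The article states a criterion for all tests, prescribes two analyses per outcome, CAN included, and hypothesises improvement throughout. An analysis plan would have to reverse stated text, not just fill a gap. The excess error for CAN remains with or without baseline adjustment.

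**Conclusion.** The point holds in a limited form. Followed as written, the plan gives CAN an error of about 7-9% instead of 5%, because two analyses are tested and neither is decisive. This rests only on the assumed baseline to follow-up correlation of 0.3-0.7 and on whether the total-score model adjusts for baseline CAN.

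Across outcomes, the uniform criterion makes at least one chance P<0.05 quite possible: 42-64% in either direction or 21-40% for false benefit, with one test each, and higher with both dependent variables. These figures depend on an assumed count of about 20, which includes CAN and takes three cytokines that the article offers only as examples, and on assumed correlations.

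The naming of CAN as sole primary outcome limits the harm if conclusions rest on it alone. The article does not say that they will, and its closing hypothesis in the Background is at odds with the exploratory wording a few lines above. This should be corrected; it does not undermine the design.

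**What to change.** - In Statistical analysis, apply the P<0.05 criterion to one pre-named between-arm analysis of CAN, for example the 3-month total score adjusted for baseline CAN. The change-score analysis can stay as a supporting check.
- Report each secondary outcome from one model, as a supportive estimate with a 95% confidence interval and without a confirmatory claim of significance. Treat the within-arm paired comparisons as descriptive.
- In the Background, limit the hypothesis of improvement to CAN, so that it agrees with the exploratory wording of the secondary aims.

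With one decisive analysis the error for CAN returns to 5%. The cost is wording only: no change to patients, data or procedures. The downside is that secondary outcomes lose the label of significance.

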## Discussion

A Cochrane review from 2010 concluded that exercise interventions for schizophrenia are feasible and may have beneficial psychobiological effects [33]. However, only three studies fulfilled the review inclusion criteria with small sample sizes of 12, 13 and 61 patients, respectively. A recent systematic review and meta-analysis including eight studies showed only a modest increase in levels of exercise and no changes in symptoms or body mass index following exercise [34]. However, the studies varied widely in exercise treatments, sample size, age-range and outcomes measured. Only two studies used a validated measure of exercise as the primary outcome, the 6-minute walking test. Moreover, exercise intensity was not measured; thus, benefits of the interventions were difficult to compare [34]. The effects of exercise on cognition in psychosis have rarely been studied. One study reported a 34 percent improvement in short-term memory, but included only eight patients and eight controls [35].

The treatment potential for exercise in psychosis is large because most individuals with the disorder are sedentary and inactive. This study will be one of the first to comprehensively assess the health-related effects of regular exercise in young adults with psychosis. Exercise interventions for this patient group need to be carefully adjusted and supervised; motor coordination and sensory integration may be impaired, which can adversely affect coordination and body awareness [36]. Supervision of exercise programs has been shown to increase adherence and improve outcomes in depression studies [37]. For these reasons, the current study will involve closely supervised, tailored exercise sessions that will be adjusted to meet patient needs. The objective assessment of physical activity is another important design consideration, as memory and recall may be impaired. Some novice exercisers could be unfamiliar with the sensation of aerobic activity, and may interpret these feelings as distress or anxiety. Care will be taken to ensure that novice exercisers begin with low-intensity exercises so they have time to become familiar with the physical and affective changes often associated with exercise [38]. All classes will be supervised by qualified exercise-trainers, and a psychiatric nurse will be readily available should patients feel distressed or require assistance. While psychosocial interventions in psychosis have expanded rapidly in recent years, exercise interventions have received less attention. Results will be used to inform clinicians and researchers about the feasibility and effects of exercise as an adjunct treatment for psychosis.

